   1. STUDY DESIGN

The study is an observational prospective cohort study with patients of four chronic disease areas with existing DMPs (asthma, chronic obstructive pulmonary disease (COPD), diabetes (type 1 and type 2) and coronary artery disease) with two sub-cohorts (DMP and non-DMP) for each disease.

- Type of control: none / group matched BARMER insurees (matching criteria: disease area, gender, age group)
- Level and method of blinding: none
- Method of treatment assignment: stratified randomized selection of study population
- Number of subjects: 200,000 patients invited (50,000 per chronic indication and about 25,000 in each sub-cohort)
- Duration of study: one year (four quarterly survey periods)

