  1. INTERVENTION

In addition to filling out the survey questions at four points in time (intervention 1), all participants will receive PRO feedback as a potential nudge (intervention 2). The PRO feedback will be a pdf report sent via email and available in their study participant profile, which graphically (line charts) shows the patients’ individual generic and disease-specific health status in comparison to the individual peer group. In addition to the visual feedback, the results will shortly be explained on the same page. The description will cover whether patient-individual PRO scores are better or worse compared to the peer group, and for longitudinal values, whether patient-related changes improved or worsened. Additional details on the scores, sub-scores, and calculations are shared with the patients on the following pages of the report. Peer groups are classified according to their disease, gender, and age group. The peer group is created based on individuals who have replied to the previous survey and will only be displayed if the group consists of at least four individuals. This threshold is set by the German General Data Protection Regulation. The report refers to the patients’ physicians as the main contact to discuss the results or in case of questions.

- 1. SAMPLE SIZE

The sample is drawn stratified randomly from insured patients of one large German statutory health insurance with about 9 million insured persons (of about 73 million statutorily insured persons in total in Germany) according to their diagnosis and/or disease management program status. A one-to-one matching of participants of one DMP with non-participants of a DMP but with the same proven diagnosis according to the ICD-10-GM system is made. Further stratification criteria are age group, gender, and health system utilization.

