As shown in Figure 1, the first point of contact will be a letter from the insurance to insured individuals with chronic diseases, who can then sign into the digital study via a QR code or link. For each of the different disease areas, a distinct care path is opened, with a sign-in process followed by selected PROMs and PREMs. The study covers a timeframe of one year with four overarching time intervals with dedicated questions. These are split into smaller tasks to facilitate the answering process for participants. The time intervals are split into smaller tasks to facilitate the answering process for participants. A few weeks after responding to the first set of questions (A & B), patients will receive a report with their individual PROM scores compared to a peer group, the PRO feedback (C). From the second interval onwards, patients will also receive the PRO feedback in a longitudinal visualization. Lastly, following the PRO feedback participants will be surveyed regarding their health behavior (D).

Figure 2 presents the questionnaires that will be used in the study per chronic disease group. PROM surveys include generic as well as disease-specific PROMs. The participants will receive individual reports on their patient-specific and peer group outcomes (PRO feedback) and will be asked about the comprehensibility of the report. Following the report, the participants receive a set of questions regarding the report’s comprehensibility and their health-related behavior.

[figure not shown]

*Figure 2: Survey items in the PROMchronic trial*

The primary data collected in this study is hence:

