**For the third research question:**

- Comprehensibility of PRO feedback
- Helpfulness of PRO feedback
- Impact of PRO feedback on healthcare behavior overall and per subdimension

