- Using machine learning predictive models (long-short-term memory deep learning network for time trend classification, random forest, logistic regression, decision tree and/or support vector machine) to identify admission risk in Q3 and Q4 based on PROMs/PREMs in Q1 and Q2

*PRO feedback*

- Mainly: Statistically significant change in at least one of the health care behavior dimensions (see 4.2) and comparison of participants who opened the report vs. those who did not, using logistic regression (change/no change)
  - Physical activity: Shift of participants to a higher category
  - Nutrition: Shift of participants to “More healthy” from any other category
  - Tobacco: Shift of participants to a lower category
  - Alcohol: Shift of participants to a lower category
  - Sleep: Share of stable participants (no significant variation in sleep duration)
- Secondly: Descriptive exploratory analysis of the rates of the following two evaluation dimensions and statistically significant differences in subgroups (see 5.1 and 4.3):
  - Understandability
  - Helpfulness
  - Emotional change

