**Data analysis**

- Check for normality using the Shapiro–Wilk test
- Check for intraclass correlation using intraclass correlation coefficients
- Analyze missing data
- Descriptive statistics of patient and treatment characteristics
- Time series analysis
- Parametric and non-parametric methods
- Statistical tests depending on normality for the primary and secondary outcomes to compare:
  - Responders vs. non-responders (to the nudge)
  - DMP vs non-DMP members
- Linear and logistic regressions controlling for:
  - Significant patient characteristics
  - Significant other collected variables depending on the research question

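### Section 5.2 tests outcomes between responders and non-responders to the nudge, an undefined grouping formed after a report that everyone receives, so an apparent benefit can arise with no report effect

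*Protocol*

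**What the plan says.** The Data analysis list in section 5.2 calls for "Statistical tests depending on normality for the primary and secondary outcomes to compare" two pairs of groups. The first pair is "Responders vs. non-responders (to the nudge"); the second is DMP against non-DMP members. Section 5.1 sets the significance level at 0.05, two-sided.

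The nudge is identified in section 2.4: "all participants will receive PRO feedback as a potential nudge (intervention 2"). Section 2.1 gives the control as "Type of control: none / group matched BARMER insurees (matching criteria: disease area, gender, age group"). On timing, section 2.6 states: "Lastly, following the PRO feedback participants will be surveyed regarding their health behavior (D").

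Section 4.2 lists among the secondary outcomes "Impact of PRO feedback on healthcare behavior overall and per subdimension". In section 5.2, the PRO feedback analysis specifies a "comparison of participants who opened the report vs. those who did not, using logistic regression (change/no change"), with change defined by items such as "Physical activity: Shift of participants to a higher category".

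Nowhere does the protocol say what makes someone a responder to the nudge. The responder terms in section 4.2 (first, regular, full) refer to completing survey periods.

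**The concern.** No group in the cohort goes without the report. The matched insurees could serve as a comparison for claims data, but they supply no survey outcomes. Any split by reaction to the report is therefore made by the participants themselves, after it was sent.

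Section 1.2 asks whether feedback can lead to positive behavioural change, which is a causal question. A significant difference between nudge responders and non-responders would easily be taken as an answer. The contrast cannot give one, because the groups may differ through recovery, motivation or health, whatever the report does. With thousands of participants, even a weak shared cause is enough for significance.

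**Working it through.** **Expected sample size.** Section 2.5 gives 200,000 invited, 30% reacting, two-thirds of these allowing follow-up, and 40% of these completing all follow-ups. 200,000 × 0.30 × 2/3 × 0.40 = 16,000, which matches the protocol. Spread evenly over four disease areas this is 16,000 / 4 = 4,000 each; the even spread is an assumption. The protocol gives no effect size or power for the nudge contrast.

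**Reading A: responder = changed behaviour.** For the behaviour outcome itself no calculation is needed, since the groups are defined by the outcome being tested.

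For PROM change, assume (none of this is in the protocol):
- no report effect;
- responders are the top 15% on behaviour change;
- behaviour change and PROM change are bivariate normal with correlation r = 0.1, 0.2 or 0.3, arising from common causes such as recovery.

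Steps:
1. The cut-off for the top 15% is 1.036, where the normal density is 0.2332.
2. Mean gap in PROM change, in overall SDs: r × 0.2332 / (0.15 × 0.85) = 1.829 × r, giving 0.183, 0.366 and 0.549.
3. Within-group SD: √(1 − 0.15 × 0.85 × gap²) = 0.998, 0.991 and 0.981. Dividing gives standardised differences of 0.18, 0.37 and 0.56.
4. Standard error with 16,000: √(1/2,400 + 1/13,600) = 0.0221. With 4,000: √(1/600 + 1/3,400) = 0.0443.

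| r | Difference (SD) | z, n = 16,000 | z, n = 4,000 |
|---|---|---|---|
| 0.05 | 0.09 | 4.1 | 2.1 |
| 0.1 | 0.18 | 8.3 | 4.1 |
| 0.2 | 0.37 | 16.7 | 8.3 |
| 0.3 | 0.56 | 25.3 | 12.6 |

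A simulation with other assumptions points the same way (30% responders, test-retest correlation 0.7, no report effect, 300 runs per setting, two-sided t-test at 0.05, counting significant results in favour of responders). At r = 0.05, 0.1 and 0.2 a false benefit appeared in 67%, 100% and 100% of runs with 4,000, and in 100% of runs at all three with 16,000. At r = 0 the rate was about 3%, close to the nominal 2.5% in that direction.

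The size of the responder group is itself open to chance. If a responder is anyone with a favourable shift in at least one of five behaviour dimensions, and chance shifts occur independently with probability q in each, the share is 1 − (1 − q)⁵. For q = 5%, 10% and 15% that is 23%, 41% and 56%.

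**Reading B: responder = opened the report.** Assume 60% open it, the report does nothing, and an unmeasured motivation factor has the same loading on opening and on improvement. Share of runs with a false benefit, same test:

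| Loading | n = 4,000 | n = 16,000 |
|---|---|---|
| 0 to 0.05 | 2–3% | 2–4% |
| 0.1 | 6% | 17% |
| 0.2 | 53% | 99% |
| 0.3 | 99% | 100% |

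For a binary outcome with the same 60/40 split, a change rate of 22% against 20% due to motivation alone is significant with probability 0.33 at 4,000 and 0.86 at 16,000.

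**The case against.** The strongest reply is that the term is undefined and may be shorthand for opened versus not opened, the only nudge grouping the protocol spells out. Circularity then falls away and ordinary self-selection remains. This stands, and it is why the point is put conditionally.

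A reader might infer that a benefit is bound to appear whatever the report does. The protocol does not support that. Near-certainty needs both the behaviour-change definition and a non-zero correlation with the outcome, and the protocol states neither. Under the opened reading with a loading of 0.1, a false benefit appears in only 6% to 17% of runs.

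It is also fair that 15% responders and r = 0.1 to 0.3 are assumed, and that PROM change is to be analysed per disease area, where z is about half the pooled value.

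Three further replies carry less weight. An SAP might define the term, but any definition based on reaction to the report still groups people by a post-report event. The regressions adjust for significant characteristics, but this cures neither circularity nor unmeasured motivation. The study is observational, but this line orders significance tests and carries no descriptive label, although section 5.2 uses such a label for other PRO feedback items.

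**Conclusion.** The point holds in conditional form. Under either plausible reading the groups are self-selected after a report that everyone receives, so the planned tests cannot show what the report does.

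- **Changed behaviour:** the test on behaviour outcomes is circular. Under the stated assumptions, other outcomes could show a spurious difference of about 0.18 to 0.56 SD, with z of about 8 to 25 for all 16,000 and about 4 to 13 in a disease area of 4,000.
- **Opened the report:** a spurious benefit is possible but not assured. Its chance runs from near the nominal rate to near certainty, depending on how strongly motivation drives both opening and improvement.

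These sizes illustrate the problem; they do not predict the trial's results. That the contrast cannot isolate a report effect does not depend on them.

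**What to change.** Amend the responder line in the Data analysis list of section 5.2:

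- State what a responder to the nudge is.
- Do not test outcomes between groups defined by behaviour change after the report. Use that grouping only to describe which pre-report characteristics predict response.
- If opened versus not opened is meant, say so. Take outcomes measured after opening, and adjust for pre-specified pre-report characteristics, including the baseline value where one is collected. Section 2.6 places the behaviour survey after the report, so check whether a pre-report behaviour value exists. Report the result as a non-causal association.

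The change is confined to that entry and needs no new data. The cost is the loss of a nominal significance test and a weaker statement on the benefit of feedback.

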**Patient reported indicators:**

- Generic PROM index score: PROMIS PROPr is a preference-based score which combines seven PROMIS domains of health status into one score (cognitive function, depression, fatigue, pain, physical function, sleep, social roles)
- Disease-specific PROM index scores for each chronic disease

Asthma: Asthma Impairment and Risk Questionnaire (AIRQ) score

COPD: Clinical COPD Questionnaire (CCQ) score

Diabetes: Problem Areas in Diabetes (PAID-5) score

Coronary artery disease: Seattle Angina Questionnaire (SAQ-7) score and Rose Dyspnea Scale (RDS) score

- PREM index score: Responsiveness of the health care system
- Looked at PRO feedback
- Comprehensibility of PRO feedback
- Helpfulness of PRO feedback
- Emotional reaction to PRO feedback
- Discussion of PRO feedback with physician(s)
- Health behavior in five dimensions:

Physical activity

Nutrition

Tobacco consumption

Alcohol consumption

Sleep duration

- Plans to change health behavior in the future
- Trigger for health behavioral change
- Overall health improvement
- Disease-specific health improvement

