   1. GENERAL METHODOLOGY

Quantitative variables will be described as mean (respectively median), standard deviation (inter-quartile range), number, and rate of missing data, and compared between arms with a t-test, or if not appropriate with a Wilcoxon rank-sum test. Qualitative variables will be reported as absolute and relative frequencies, number, and rate of missing variables, and compared between sub-cohorts with the Chi-square test or the Fisher’s exact test. Variables will be compared between both sub-cohorts (DMP and non-DMP participants). P-value <0,05 with a bilateral hypothesis will be considered significant. All the analyses will be carried out using R, SAS, and other statistical software for Windows.

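### Covariates are chosen by significance and DMP groups are compared by unadjusted tests, so the sampling factors are not guaranteed a place in the models and post-report variables are not excluded

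*Protocol*

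**What the plan says.** Section 2.5 (Sample size) pairs DMP participants one-to-one with non-participants who have the same diagnosis, and adds: "Further stratification criteria are age group, gender, and health system utilization". Section 5.2 (Primary Outcomes) expects participation to vary by gender, age, diagnosis and utilization. It answers this with weighting, but only for the representativeness analysis.

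For the comparison of the two sub-cohorts, section 5.1 has quantitative variables "compared between arms with a t-test, or if not appropriate with a Wilcoxon rank-sum test" and qualitative variables "compared between sub-cohorts with the Chi-square test or the Fisher’s exact test". The Data analysis list in section 5.2 repeats this as "Statistical tests depending on normality for the primary and secondary outcomes to compare" DMP with non-DMP members. The same list then names linear and logistic regressions controlling for "Significant patient characteristics" and "Significant other collected variables depending on the research question".

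The protocol does not say what a covariate must be significant against, whether DMP status is the exposure in these regressions, or whether the tests or the regressions carry the DMP conclusion. The collected variables in section 2.6 include helpfulness of the report, emotional reaction to it and discussion of it with physicians. All of these arise after the report is sent.

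**The concern.** Three things follow from this wording.

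- **Unadjusted DMP contrast.** Balance on the sampling factors is arranged among those invited. The analysis uses those who respond. If the response pattern differs between DMP and non-DMP patients, the responders are no longer balanced, and a t-test or chi-square test attributes the difference to DMP status.
- **Selection by significance.** Whether a factor is adjusted for depends on the sample size and the data at hand. The adjustment can then differ between diseases and subgroups, and the reported intervals ignore the selection.
- **Timing of covariates.** The main PRO-feedback analysis is a logistic regression of behaviour change, comparing patients who opened the report with those who did not. A variable that follows opening may lie on the path from opening to behaviour. Adjusting for it removes part of the effect under study.

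At stake are the DMP versus non-DMP results for outcomes and experience, and the report-opening result. The primary endpoint, representativeness, has its own weighting and is not the target here.

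**Working it through.** **1. Group sizes (section 2.5).** The protocol's own figure reproduces: 200,000 × 0.30 × 2/3 × 0.40 = 16,000 complete data sets, or 8% of those invited.

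- All full responders: 16,000 / 2 = 8,000 per DMP group.
- Full responders in one disease: 16,000 / 8 = 2,000 per DMP group.
- All initial responders: 200,000 × 0.30 / 2 = 30,000 per DMP group.

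These assume equal response in both groups.

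**2. What remains of the pairing.** There are 100,000 invited pairs. If the members of a pair respond independently (assumption), 100,000 × 0.30² = 9,000 pairs are intact at first response and 100,000 × 0.08² = 640 at completion. Pairing cannot carry the analysis, so the factors have to be handled in the model. Losing pairs does not by itself unbalance the groups.

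**3. Bias of the unadjusted contrast.** Bias = imbalance × slope. The protocol gives neither, so both are assumptions.

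- Central case: 0.1 × 0.3 = 0.03 SD.
- Range: 0.05 × 0.2 = 0.01 SD to 0.2 × 0.4 = 0.08 SD.

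The standard error is √(2/n) in SD units. The chance of rejecting a true null at two-sided 5% is Φ(−1.96 + bias/SE) + Φ(−1.96 − bias/SE).

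| n per group | SE | Smallest significant difference (1.96 × SE) | Bias 0.01 | Bias 0.03 | Bias 0.08 |
|---|---|---|---|---|---|
| 2,000 | 0.0316 | 0.062 | 6% | 16% | 72% |
| 8,000 | 0.0158 | 0.031 | 10% | 47.5% | >99% |
| 30,000 | 0.0082 | 0.016 | 23% | 96% | >99% |

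In a simulation at 2,000 per group with no true effect, a 0.2 SD imbalance gave rejection rates of 0.10, 0.22 and 0.47 for slopes of 0.1, 0.2 and 0.3. With the factor always in the model the rates were 0.06, 0.05 and 0.05.

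**4. If balance held exactly.** The plain test is then conservative, with true level 2 × [1 − Φ(1.96/√(1 − R²))]. For R² of 0.1, 0.2 and 0.3 (assumed) this is 0.039, 0.028 and 0.019. Power is 77%, 73% and 68% where the adjusted model has 80%. Adjustment is preferable in either case.

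**5. Selection by significance alone.** The same simulation kept the covariate only if p < 0.05.

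- At 2,000 per group, a covariate with slope 0.05 was dropped in about 10% of runs and one of 0.1 or more in none. The error rate was 0.03 to 0.06.
- At 100 to 250 per group, a covariate with slope 0.1 was dropped in about 70% and 40% of runs respectively. The error rate reached about 0.07, at imbalances up to 0.5 SD.

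**6. A covariate measured after exposure.** Assume a direct effect of 0.10 and a path of 0.3 × 0.3 through the later variable. The total effect is 0.10 + 0.09 = 0.19, and adjusting for the later variable leaves 0.10. Now let an unmeasured cause with weight 0.4 affect both the later variable and the outcome. The coefficient of the later variable is inflated by 0.4² / (0.4² + 1) = 0.138, and the estimate falls to 0.10 − 0.3 × 0.138 = 0.06.

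**The case against.** **Dropped factors.** A reader might infer that significance selection will routinely discard the sampling factors within each disease. At the planned size it will not (step 5). The effect is confined to small subgroups and is modest there.

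**Broken balance.** A reader might also infer that differential response has already unbalanced the DMP groups. The protocol says only that participation varies by gender, age, diagnosis and utilization. It does not say that the pattern differs by DMP status. Response that depends on age equally in both groups dissolves pairs and leaves the groups comparable on age. Group-specific response is plausible but is an assumption.

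**Post-report covariates.** No section names such a variable as a covariate, helpfulness is listed as an outcome in section 4.2, and the choice is to depend on the research question. Helpfulness also has no natural value for someone who never opened the report. Entry of these variables is therefore permitted, not planned.

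**Descriptive aim and level of detail.** The secondary objective asks how results differ by DMP participation, and an unadjusted comparison answers that descriptively. Regressions are listed as well, and full covariate lists commonly belong in an SAP.

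The first three objections stand and limit the point. The last stands in part. Unadjusted tests are fair as description, but the protocol attaches a significance threshold to them and does not say which result leads. The covariate rule is not left open either: the protocol states one, and an SAP that follows it inherits it.

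**Conclusion.** The point holds in a limited form, as a change that should be made. The protocol states a significance-based covariate rule and unadjusted DMP tests. Neither secures the factors on which its own sample was drawn, and nothing excludes variables that follow the exposure.

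The larger risk lies in the unadjusted DMP contrast and grows with sample size. At the central assumed bias of 0.03 SD it is small within one disease among full responders and severe among all initial responders. At 0.03 SD the bias is about half the smallest significant difference at 2,000 per group, just below it at 8,000 and nearly twice it at 30,000. These figures rest on an assumed imbalance and slope, and on a response pattern that differs by DMP status. They measure the unadjusted test, not the selection rule. The loss from a post-report covariate is likewise illustrative.

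**What to change.** In the Data analysis list of section 5.2, replace the two significance-based entries with wording to this effect:

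- Every regression includes disease (where diseases are pooled), age group, gender and the utilization stratum used for sampling, whatever their p-values. DMP status is the exposure in the DMP contrast and a covariate elsewhere.
- Further covariates come only from a prespecified list of variables measured before the exposure in question. For the report-opening contrast this excludes helpfulness, emotional reaction and discussion with the physician. For the DMP contrast, survey BMI is not forced in, because height and weight are reported after DMP status is established.
- The unadjusted tests of DMP against non-DMP are descriptive. The DMP inference comes from the adjusted model.

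The wording should name the factors explicitly, because section 2.1 lists disease area, gender and age group as matching criteria for the insurer's control group, while section 2.5 adds utilization for the sample. The utilization stratum should be the one fixed at sampling. If it may itself reflect earlier DMP enrolment, that should be acknowledged when the DMP estimate is interpreted.

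The cost is one paragraph of wording and slightly more analysis. The sampling factors are already held for everyone, so no new data are needed.
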